#### Additional variables

Socio-demographic and medical variables are gathered to provide insight into the characteristics of the sample and to interpret the outcomes of the study.

*Socio-demographic variables *age, gender, marital status and educational level are assessed directly after the first consultation with the radiotherapist (T2).

*Medical variables *before RT include cancer site, adjuvant chemo-treatment, TNM-classification and Karnofsky Performance Index (KPI). The TNM-classification is a systematic way of describing the size, location and spread of a tumour. Once established, it must remain unchanged in the patient's record because the definitive TNM-classification is determined just before either initiation of treatment or making the decision not to treat [51]. The KPI emphasises physical performance and dependency. The scale is weighted towards physical dimensions of quality of life rather than social and psychological dimensions. Patients are assigned to categories by a physician. The KPI takes no account of the patient's feelings. The KPI varies from 100 (normal, no complaints, no evidence of disease) to 0 (dead) [43]. Medical data are extracted from patient records.

#### Process evaluation

The aim of the process evaluation is to gain insight into factors potentially influencing the effectiveness of using the SIPP and factors facilitating future implementation of the SIPP. Process evaluation data are collected using self-developed questionnaires completed by patients of the intervention groups directly after their first consultation with the radiotherapist and by radiotherapists directly after the first consultation and twice during the total recruitment period of patients. Table 2 provides a short overview of process evaluation measures. The process evaluation outcome measures are:

**Table 2 T2:** Outcome measures of the process evaluation

Variables	No. of items	T1	T2	T3	T4
Radiotherapists' opinion about the usefulness of the SIPP in general	9	-	-	-	Q
Radiotherapists' opinion about the usefulness of the SIPP after first consultation	4	-	Q	-	-
Radiotherapists' suggestions for improvement of the intervention or other remarks	2	-	-	-	Q
Patients' opinion about the usefulness of the SIPP after first consultation	3	-	Q	-	-
Patients' suggestions for improvement of the intervention or other remarks	2	-	Q	-	-

T1: Before first consultation (baseline, only groups with pre-measurement); T2: After consultation;

T3: Three months after baseline; T4: 12 months after baseline; Q = questionnaire.

• nine items on the opinion of radiotherapists about the usefulness of the SIPP in general, e.g. "Did you find discussing the SIPP with the patient useful?" (item range 0 (not useful) to 10 (very useful));

• four items on the opinion of radiotherapists about the usefulness of the SIPP after each consultation with a specific patient, e.g. "How much extra time (in minutes) does discussing the results of the SIPP take?";

• opinion of the patients about the usefulness of the SIPP after the first consultation, e.g. "Did you find discussing the SIPP with the radiotherapist useful?" (item range 0 (not useful) to 10 (very useful); and

• two open questions for suggestions for improvement of the intervention or other remarks.

### Statistical analysis

Descriptive techniques will be used to describe patients' background characteristics. To detect potential differences between the experimental and control groups at the start of the study, the baseline levels of psychological distress and quality of life will be compared. Furthermore, to identify potential differences between the two experimental groups and the two control groups (both with and without pre-measurement) at T3 the extent of psychological distress and quality of life will be compared. If these latter differences emerge, the four groups need to be handled separately in the analyses, i.e. the experimental and control groups with pre-measurement and the experimental and control groups without pre-measurement will be compared separately. If not, the two experimental groups and the two control groups will be combined in one group.

Data of the effect evaluation will be analysed according to the intention-to-treat principle. Univariate, multivariate and descriptive techniques are applied to estimate the effect of the intervention by comparing the experimental with the control groups with regard to the primary and secondary outcomes at the follow-up measurements and by comparing the pre-test (T1) with post-tests (T3 and T4). Potential confounding factors and baseline differences will be checked and included in the model if necessary. Since dependency between outcome variables from the same cluster may exist, as well as between repeated measurements within patients, multilevel modelling will be carried out. Furthermore, multilevel modelling minimizes the loss of data through dropout by including all available data from participants in the analyses. Dropout will be described.

The process evaluation data (collected from radiotherapists and patients of the experimental groups) will be analysed by means of descriptive techniques.

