#### Primary outcome measures

The primary outcome measures are the number and types of referrals of patients with psychosocial problems to psychosocial workers at the Institute Verbeeten and/or to external health care providers (e.g. psychologists, psychiatrists). The number and types of referrals to (psychosocial) caregivers are measured at three months (T3) and 12 months (T4) after baseline assessment with a self-developed questionnaire by the patient and from registration records of the psychosocial caregivers at the Institute Verbeeten. This questionnaire comprises eight items on whether the patient is referred to a psychosocial caregiver and the types of problems the patient has experienced (e.g. financial, psychological, and sexual). The psychosocial caregivers at the Institute Verbeeten collect data from all referred patients, including types of problems, number of sessions needed and further referral to an external (psychosocial) caregiver.

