#### Secondary outcome measures

The secondary outcomes are classified in three dimensions: 1) patients' satisfaction with the radiotherapist-patient communication during the first consultation; 2) extent of psychological symptoms at T3 and T4; and 3) patients' quality of life at T3 and T4.

*Patients' satisfaction with the radiotherapist-patient communication *is measured directly after the first consultation with the radiotherapist (T2) by the patient completing a self-developed questionnaire comprising five items. The first four items measure whether physical complaints, psychological complaints and social and sexual problems were discussed with the radiotherapist (item range 1 (yes) to 3 (no) plus "not applicable"). The fifth item measures the patient's general opinion (item range 1 (very bad) to 6 (very good)) about the communication with the radiotherapist during the first consultation.

*The extent of psychological symptoms *is measured with the Hospital Anxiety and Depression Scale (HADS) [16] and the Goldberg's General Health Questionnaire-12 item version (GHQ-12) [17]. Patients complete these self-reported questionnaires at baseline and at T3 and T4.

The HADS is a valid, reliable and useful instrument [16] that is widely used in studies among cancer patients [34-40]. It is considered unbiased by coexisting general medical conditions because its questions do not refer to somatic symptoms associated with depression [41]. The HADS consists of a brief subscale of anxiety and a subscale of depression. Both subscales comprise seven items. Ratings by patients are made on four-point scales (0–3, with 3 indicating greatest distress). Higher scores on each subscale indicate a greater presence of problems [16,42,43].

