The GHQ-12 is a well-validated instrument [17] that has been used in numerous studies among cancer patients [34,36,44,45]. It is a standardised measure of psychiatric morbidity across a wide range of patients [43]. It was intended for use in general practice settings as a screening instrument for detecting verifiable psychiatric morbidity (generally anxiety and depression). It measures "usual state" rather than chronic (long-term) problems [43]. The GHQ assesses with 12 items whether the patient considers him- or herself better, the same, worse or much worse over the previous four weeks than he/she "usually" is. Those who indicate that their symptoms are unchanged or have decreased receive a score of 0, while those who report that their symptoms have increased receive a score of 1. Total scores range from 0 to 12 [17].

*Quality of life *is measured using the European Organisation for Research and Treatment of Cancer, Quality of life Questionnaire (EORTC QLQ-C30) [46]. The EORTC QLQ-C30 is validated and widely used [30,47-50]. It is a 30-item cancer-specific measure that assesses health-related quality of life. The EORTC QLQ-C30 comprises:

• five functional subscales: physical (five items), role (two items), emotional (four items), cognitive (two items) and social functioning (two items);

• a subscale about global health status and quality of life during the past week (two items);

• three symptom scales: nausea/vomiting (two items), fatigue (three items) and pain (two items); and

• six single items measuring appetite loss, insomnia, constipation, diarrhoea, dyspnoea and financial difficulties due to illness or treatment.

The items on the five functional scales and three symptom scales have four-point response choices of 1 (not at all), 2 (a little), 3 (quite a bit) and 4 (very much). Categories 3 and 4 are regarded as indicators of clinically-significant symptom levels. Both items of the subscale about global health status and quality of life use a seven-point visual analogue scale (VAS) ranging from 1 (very poor) to 7 (excellent) [43]. Patients completed the self-reported questionnaire EORTC QLQ-C30 at baseline and at T3 and T4.

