## Discussion

This study will provide insight into the actual systematic effects of using the SIPP in consultation settings. It is important to know the possible effects of using the SIPP on aspects such as communication between physicians and patients, early recognition and treatment of psychosocial problems, the extent and severity of experienced psychological problems among cancer patients and the quality of life of patients over a long period. Until now, there have been no RCTs on the effectiveness of the SIPP on aspects such as quality of life among cancer patients and the extent of psychological distress that cancer patients experience over a long period after the initial radiation or other treatment of the cancer. Until now, there have also been no reports on the differences in number of patients receiving psychosocial help because of using the SIPP.

The design of this study is a CRCT. Cluster randomisation is applied because randomisation at the patient level may jeopardise the validity of the study since patients of the experimental and control conditions may visit the same radiotherapist for consultation. Furthermore, radiotherapists may alter their communication style, attitude or may pay more attention to patients' psychosocial distress because of using the SIPP. The Solomon four-group design is chosen in order to check for potential pre-measurement effects on intervention outcomes [52,53].

In this study, we decided to include patients with the most common cancer types and with a reasonably good prognosis because patients were asked to complete questionnaires 12 months after baseline measurement.

One limitation of this study is that the results can not be generalised to all Dutch cancer patients since our study population consisted of cancer patients that received RT. Further studies outside the radiotherapy setting would be required to generalise the results.

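### Secondary outcomes at T3 decide whether the referral analysis is split or pooled, while the interaction that the Solomon design exists to check is not tested directly

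*Protocol article*

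**What the plan says.** The Statistical analysis section plans a check "to identify potential differences between the two experimental groups and the two control groups (both with and without pre-measurement"), and states that "at T3 the extent of psychological distress and quality of life will be compared". The consequence follows: "If these latter differences emerge, the four groups need to be handled separately in the analyses". In that case the pre-measured experimental and control groups are compared with each other, and the unmeasured pair likewise. If no difference appears, the two experimental groups are merged, as are the two control groups.

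The section on primary outcomes says: "The primary outcome measures are the number and types of referrals of patients with psychosocial problems to psychosocial workers" (and external providers), measured at T3 and T4. Distress (HADS, GHQ-12) and quality of life (QLQ-C30) are listed as secondary. The Discussion gives the purpose of the design: "The Solomon four-group design is chosen in order to check for potential pre-measurement effects on intervention outcomes".

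**The concern.** The rule governs every effect analysis, including the primary one, and has three weaknesses.

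- **Outcome.** Only secondary outcomes feed the decision. Referrals play no part in it, yet their analysis is settled by it.
- **Contrast.** A pre-test matters for the intervention effect if it changes that effect, which is a condition by pre-measurement interaction. The rule names no such term.
- **Selection.** Data collected after the intervention choose the analysis, and the same trial data then supply the result. Ordinary p-values and intervals ignore that step.

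At stake are which comparison counts as primary, how precise it is, and what is concluded if two separate comparisons disagree.

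**Working it through.** **1. The two readings of the rule.** The sentence describing the check is ambiguous.

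- *With v without pre-measurement inside each arm (the natural reading).* Let the pre-test shift the mean by a in the control arm and by a + g in the experimental arm. The rule looks at a and at a + g. If g = 0 and a is not zero, both comparisons tend to trigger a split. The pooled contrast is unbiased, because odd/even-week allocation gives both arms about the same share of pre-measured patients and a cancels. The quantity that matters, g, is never tested directly.
- *Experimental v control.* A real intervention effect on distress or quality of life would itself trigger the split.

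**2. The planned sample size.** Inputs from Sample size and power analysis: 2% v 11% referred, 80% power, one-sided 0.05, design effect 1.13, 20% dropout.

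n = [z(0.95)·√(2·p̄·q̄) + z(0.80)·√(p1q1 + p2q2)]² / (p2 − p1)², with p̄ = 0.065

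= [1.645 × 0.3486 + 0.842 × 0.3428]² / 0.09² = 0.743 / 0.0081 = 91.7, so 92 as stated.

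4 × 92 = 368; 368 × 1.13 = 415.84; 415.84 / 0.80 = 519.8, so 520 as stated. The trial was therefore sized at 92 in each of four groups. About 416 patients are analysed, 104 per group, which is 92 after dividing by 1.13.

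**3. Power with and without a split.** Power = Φ{[0.09·√n − 1.645 × 0.3486] / 0.3428}.

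- Pooled, n = 184 per arm (208 / 1.13): Φ(1.89) = 0.97.
- Split, n = 92 per arm in each half: Φ(0.85) = 0.80.

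If smaller clusters within each half lower the design effect to about 1.07 (an assumption), n = 104 / 1.07 = 97 and power is 0.82. Against a 2% control rate, the experimental rate detectable with 80% power is about 7.5% pooled and 11% in each half.

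**4. Chance of a false split.** The article names 2 HADS subscales, 1 GHQ-12 total and 15 QLQ-C30 scores (5 functional, 1 global, 3 symptom, 6 single items), 18 in all. It states no test or threshold. Assumptions: two-sided 5% tests, one significant result suffices, no true pre-measurement effect, with v without compared in both arms. For k independent tests the chance is 1 − 0.95^k. Correlated scores were simulated with a common correlation of up to 0.7.

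| Scores tested per arm | Tests | Independent | Correlation 0.7 |
|---|---|---|---|
| One joint test | 2 | 9.75% | not applicable |
| 2 (one distress, one quality of life) | 4 | 19% | 16% |
| 4 (HADS × 2, GHQ-12, global) | 8 | 34% | 24% |
| All 18 | 36 | 84% | 48% |

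For all 18 scores the figures at correlation 0.3 and 0.5 are 76% and 64%.

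**5. Sensitivity of the check.** With 104 per group, a true 0.2 SD difference in one arm has standard error √(2/104) = 0.139 SD. The ratio is 1.44 and two-sided 5% power is 30%.

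**6. After a split.** Treating the halves as independent, the chance of at least one false success in two one-sided 5% tests is 1 − 0.95² = 9.75% if either success counts, or 0.05² = 0.25% if both are required. With a true 2% v 11% effect, both halves succeed with probability 0.80² = 0.64.

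**The case against.** A reader might infer that a split leaves the primary comparison underpowered because it halves the data. The documents do not support this. Each half was sized at 92 v 92 for 80% power, so what is lost is the surplus that pooling would bring.

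A reader might also infer that chance will probably split the trial. That needs the assumption that any one of 18 scores at p < 0.05 suffices. The article says neither this nor what level applies, and such detail may sit in an analysis plan that is not shown. One joint test per arm would bring the rate down to about 10%. Likewise, the 9.75% joint error holds only if success in either half counts, which the article does not say.

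Looking for a testing effect on HADS, GHQ-12 and QLQ-C30 is reasonable in itself. Table 1 shows these are the instruments given at T1, whereas referrals have no T1 measure. Comparing pre-measured with unmeasured patients in each arm also gives indirect information on the interaction.

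Finally, an interaction test is weak too. For a 0.2 SD effect in one arm only, the standard error is √(4/104) = 0.196 SD and power about 17%, below the 30% of the within-arm comparison.

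These points limit the size of the problem but do not remove it. A threshold in a separate plan would not change which outcomes and which contrast drive the decision, and planned power in each half does not say which half answers the primary question.

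**Conclusion.** The concern holds as a fault in a rule that the article states, not as a complaint about missing detail. Secondary outcomes at T3 settle the form of the referral analysis. An equal testing effect (on one reading) or a real intervention effect (on the other) would cause a split. On neither reading is the interaction tested directly.

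The false-split chance is about 10% to 84%, depending on how many scores are tested and how strongly they correlate. Every figure in that range rests on an assumed two-sided 5% criterion and no true pre-measurement effect. Each half keeps the planned 80% power under the protocol's own rates, one-sided level and design effect. The losses are the pooled power of about 97%, a primary analysis fixed in advance, and a single primary answer.

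**What to change.** Delete the split-or-merge rule. Analyse all four groups in one multilevel model with condition, pre-measurement (yes/no) and radiotherapist effects. Name the condition effect averaged over pre-measurement as the primary estimate, whatever the data show. Report the condition by pre-measurement interaction, on referrals first, as an estimate with a confidence interval, and show the effects with and without pre-measurement descriptively.

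The cost is a change of analysis wording; multilevel modelling is already planned, and no extra patients or data are needed. There are two downsides. The interaction estimate will be imprecise, so a non-significant result must not be read as absence of a pre-test effect. If the interaction is large, the averaged effect has to be read beside the two stratum-specific effects.

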### Randomisation and stratification

To reduce contamination bias, radiotherapists, instead of patients, are randomly allocated to the experimental or control groups. First, the radiotherapists are stratified according to the general percentages of incoming patients they referred to a (psychosocial) caregiver in the period 2006–2007. Within their stratum, they are either randomly assigned to the experimental or to the control condition (see Figure 2). Thus, in both conditions there are equal numbers of radiotherapists who previously referred relatively more and less cancer patients to (psychosocial) caregivers. Patients are linked to their radiotherapist. Therefore, they are randomised to the experimental condition with or without pre-measurement or to the control condition with or without pre-measurement through their radiotherapist (see Figure 2). Patients who visit their radiotherapists in odd weeks are assigned to the experimental/control condition with a pre-measurement and patients who visit their radiotherapists in even weeks are assigned to the experimental/control condition without a pre-measurement. Radiotherapists of the experimental condition are asked not to discuss this study with their colleagues of the control condition.

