### Sample size and power analysis

This study is powered on the primary outcome measures, i.e. the effect of the SIPP on the number and types of referrals of patients with psychosocial problems to relevant (psychosocial) caregivers. Sample size calculation shows that 92 patients per condition are required to compare the number of referred patients to (psychosocial) caregivers between conditions with a 80% power and a significance level of 0.05 (one-sided) [28]. This calculation is based on results reported by Pruyn and colleagues [23]. In their study, the use of the Integral Checklist resulted in more referrals from 2 to 11%. This means that for our study a total of 368 patients have to be included for the analyses.

The consequence of adopting a CRCT is that the outcome for each patient can no longer be assumed as independent [26]. Such a lack of independency has implications for study size and power [29]. The standard sample size has to be inflated to take account of the cluster design by using an estimate of the Intra Cluster Correlation [30,25,26,31]. For our study, no appropriate ICC was available. Therefore, as in the CRCT of Cumming and colleagues [32], we assume an ICC of 0.005 as appropriate because the variance of our outcome measurements between clusters can be considered low compared to the variability between the patients within a cluster. To retain power, the standard sample size should be multiplied by the design effect (d, d = 1+ρ (m-1)), where m is the size of a cluster unit and ρ the ICC [25,33]. We therefore multiplied our standard sample size with a design effect (d) of 1.13. With an expected dropout rate of 20%, the corrected sample size for the CRCT is determined at 520.

It is to be noted that stratification by baseline value of the outcome variable decreases the sample size required [31]. In our study, radiotherapists are stratified according to the general percentages of incoming patients they referred to a (psychosocial) caregiver. Stratification of this primary outcome variable reduces the between-cluster variability in the primary outcome. In a study by Elridge and colleagues the sample size required decreases of almost 50% by using stratification of the primary outcome [31]. To be on the safe side regarding the power of our study we decided not to correct for stratification of the radiotherapists. Recruitment and data collection is anticipated to continue for 24 months.

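### The stratum used to randomise radiotherapists should be a fixed model term, not left to a conditional covariate check that it will tend not to trigger

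*Protocol article*

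**What the plan says.** - **Allocation.** Protocol article, Randomisation and stratification: radiotherapists are grouped by the share of incoming patients they referred in 2006-2007. "Within their stratum, they are either randomly assigned to the experimental or to the control condition". The stated result is that the two arms hold equal numbers of higher and lower referrers.
- **Link to the outcome.** Sample size and power analysis: "Stratification of this primary outcome variable reduces the between-cluster variability in the primary outcome". The same section then states that the sample size was deliberately not reduced for this.
- **Analysis.** Statistical analysis: dependence may exist within clusters, "as well as between repeated measurements within patients, multilevel modelling will be carried out". Confounders and baseline differences are to be checked and added to the model where needed. The only baseline comparison named there is of distress and quality of life. The stratum is neither named as a model term nor excluded.

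**The concern.** The covariate rule responds to imbalance and confounding. Stratified allocation exists to prevent imbalance in this one factor. The better the stratification works, the less likely the check is to admit the factor that the design says predicts referral.

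If the stratum is left out, differences between high-referring and low-referring radiotherapists count as unexplained variation between clusters. Stratification has already removed those differences from the true sampling error of the arm comparison. The estimated standard error is therefore larger than the real one: intervals are too wide, the test rejects a true null too seldom, and precision that the design has paid for is lost. Deciding after a look at the data also leaves the primary model open when it could be fixed now at almost no cost.

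**Working it through.** **1. The plan's own figures.** Rates: "the use of the Integral Checklist resulted in more referrals from 2 to 11" per cent. One-sided 5%, power 80%, pooled variance:

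n = [1.645√(2×0.065×0.935) + 0.842√(0.02×0.98 + 0.11×0.89)]² / 0.09² = 91.7, so 92.

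This agrees with "92 patients per condition are required to compare the number of referred patients to (psychosocial) caregivers between conditions with a 80% power". Then 4×92 = 368, 368×1.13 = 415.8, and 415.8/0.80 = 520. All figures reproduce. With the stated ICC ("we assume an ICC of 0.005 as appropriate"), the design effect gives m = 1 + 0.13/0.005 = 27.

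**2. Assumptions for the check.** The article gives neither the number of radiotherapists nor the stratum rates. I take 16 radiotherapists of 26 patients (416 analysable), two equal strata, four radiotherapists per stratum and arm, Solomon groups pooled, and ICC 0.005 within stratum. A cluster-level t-test stands in for the multilevel model, whose details are not stated.

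**3. Standard error without the stratum.** Let δ be half the difference between stratum rates, and v the variance of a radiotherapist's referral proportion within stratum:

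v = mean of p(1−p) × (1 + 25×0.005)/26.

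The true variance of the arm difference is 2v/8. With 8 radiotherapists per arm, the residual variance estimated without the stratum averages v + (8/7)δ². The ratio of estimated to true standard error is √[1 + (8/7)δ²/v].

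- Strata 2%/2%: δ = 0, ratio 1.00.
- Strata 1%/3%: v = 0.0195×1.125/26 = 0.000844, δ² = 0.0001, ratio √1.135 = 1.07.
- Strata 0.5%/3.5%: v = 0.019375×1.125/26 = 0.000838, δ² = 0.000225, ratio √1.307 = 1.14.

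Simulation (beta-binomial counts) agrees: about 6% to 15% too wide.

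**4. Type I error, one-sided, nominal 5%, simulated.** Without the stratum it is about 3.7% for 1%/3% (3.4-3.9% over repeat runs) and about 2.7% for 0.5%/3.5% (2.6-2.8%). With the stratum it is about 5% in both.

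**5. One-sided power at mean rates 2% versus 11%, simulated (100,000 runs; additive stratum term).** The experimental stratum rates are further assumptions.

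| Control strata | Experimental strata | Without stratum | With stratum |
|---|---|---|---|
| 2%/2% | 11%/11% | 97.3% | 97.2% |
| 1%/3% | 8%/14% | 96.0% | 97.2% |
| 1%/3% | 7%/15% | 95.3% | 97.1% |
| 0.5%/3.5% | 6.5%/15.5% | 94.5% | 97.4% |
| 0.5%/3.5% | 5%/17% | 92.2% | 97.1% |

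The loss is about 1 to 5 points. It is under 1 point if both strata gain the same 9 percentage points. It reaches about 11 points (85.7% versus 96.4%) only at the widest split with the same rate ratio of 5.5 in both strata.

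**6. Clusters and events.** 368/27 = 13.6, 416/27 = 15.4 and 520/27 = 19.3, so about 14-19 radiotherapists. At 2%, the pooled control arm has 0.02×184 = 3.7 to 0.02×208 = 4.2 referrals among analysable patients.

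**The case against.** **The rule permits the stratum.** Prior referral percentage could be admitted as a potential confounder. That stands: the plan does not exclude it. But a rule that merely allows a randomisation factor, and is geared to imbalance, is a weak way to secure its inclusion.

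**No shortfall against the planned size.** A reader might infer that the power section banks a gain from stratification that the analysis then forgoes. The documents say otherwise: no reduction was made. In every pooled setting above, power also stays over the planned 80% without the stratum.

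**Larger effects can be produced, but not from the plan's rates.** Strata of 2% and 10% make the standard error about 33% too wide. Those rates average 6%, three times the planned control rate, and imply a between-stratum ICC of 0.04²/(0.06×0.94) = 0.028, against the stated 0.005.

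**Few clusters and sparse referrals.** A reader might infer that the plan relies on ordinary large-sample inference and that its error bars are wrong. The article states no estimation method, reference distribution or degrees of freedom, and a condensed article commonly leaves these to the full protocol or SAP. The two mechanisms also oppose each other. Omitting the stratum makes the test conservative. A normal reference in place of t with 20 to 14 clusters would raise one-sided error to about 5.9-6.3%. The net direction is not determined by the document.

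**Conclusion.** The point holds in a limited form. The plan randomises within strata that it regards as related to the primary outcome, then leaves that factor to a check that balanced allocation will tend not to trigger. The consequence is lost precision and a conservative test, not a false-positive risk.

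At stratum rates averaging the planned 2%, the loss is modest, and it vanishes if the strata do not differ. These sizes rest on the assumed number of radiotherapists, two equal strata, the stratum rates, pooled Solomon groups, and a cluster-level t-test in place of the multilevel model. They show direction and order of magnitude and do not predict this trial's result. The change is worth making because it is nearly free and removes a data-driven choice from the primary model.

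**What to change.** In Statistical analysis, state that every effect model includes the randomisation stratum, or the radiotherapist's 2006-2007 referral percentage, as a fixed term whatever the baseline comparisons show. Keep the conditional check for other covariates only.

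The cost is wording plus one or two degrees of freedom with two strata. The variable is already held, since it was used for allocation. If the strata turn out not to differ, the power given up is about 0.1 point one-sided in the check above, and about one point two-sided if two degrees of freedom are spent (93.3% versus 92.4%).

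As advice only: with about 14-19 radiotherapists and about four expected control-arm referrals, name a small-sample method for the referral model, or add a within-stratum permutation check of the referral result. Making a cluster-level test primary would be a matter of preference; the document does not require it.
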